### Open questions

However, many important questions remain unanswered, even if the efficacy of CBT for symptom reduction is increasingly well established.

1. CBT for psychosis has been specifically developed for the reduction of positive symptoms. However, in contrast to more recent meta-analyses the Cochrane meta-analysis of Jones et al. [6] did not find significant reduction of positive symptoms indicating that more large scale clinical trials are needed. Wykes et al. [2] showed a significant heterogeneity in their meta-analysis which might point to unknown moderator effects. In particular the evidence for the specific efficacy of CBT should be improved. When compared to Supportive Treatment, CBT could not as yet demonstrate clear superiority.

2. Patients with psychotic disorders might conceivably experience symptom exacerbation or suicidal crises as a consequence of psychotherapeutic efforts. Negative effects should actively be sought in order to demonstrate safety of the treatment. Therefore, Jones et al. [6] recommended investigating adverse events in CBT trials. However, Tarrier et al. [7] investigated suicidality in CBT-trials and did not find any indication for an increased rate of suicide attempts. More data about treatment safety would be helpful for implementation of CBT, as scepticism among clinicians is widespread.

3. Wykes et al. [2] found that outcome in CBT trials is associated with methodological rigor. Thus, more clinical trials applying rigorous methodology are needed in order to investigate whether treatment effects are stable even in high quality studies.

4. Psychotic disorders, in particular schizophrenia, are causing a considerable economic burden, e.g. in terms of costs of care. As resources for health care a limited, the cost-effectiveness of single health services increasingly gains importance. CBT for psychotic symptoms is currently not available for a majority of patients due to therapeutic scepticism and limited resources. Against this background the question of cost-effectiveness should urgently be addressed.

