### Formal characteristics of study therapies

CBT and ST are individual outpatient treatments of 20 sessions over 9 months (7 sessions in the first seven weeks, followed by 13 fortnightly sessions)

CBT as well as ST will be conducted by specifically trained psychotherapists on the basis of a treatment manual. Each therapist conducts both the CBT and the ST treatment. In order to take responsibility as study psychotherapist, staff members have to have at least one year of clinical experience as clinical psychologist or resident in psychiatry. In addition, they have to be enrolled in formal training programs for cognitive behavioural therapy or have to have completed their formal training.

In the case of interruptions of the study therapies due to rehospitalisation of patients, holidays, other illnesses of patients, illness of therapists etc. the treatment will be continued as soon as possible. However, continuation is only possible within a time frame of 9 months after study inclusion. Thus, within 9 months after study inclusion interruptions of participation will not result in termination of the study treatment, exclusion from the study or a new screening. When continuing the treatment the remaining sessions will be scheduled on a weekly basis as long as necessary. Thus, even patients with longer interruptions will have the chance of getting a maximum of the 20 sessions. In each case, study therapies have to be terminated 9 months after study inclusion (primary endpoint).

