### Endpoints of Safety

Endpoints of safety are

• Death caused by suicide

• Suicide attempt

• Suicidal crisis (explicit plan for serious suicidal activity without suicide attempt) as defined in Calgary Depression Rating Scale for Schizophrenia [CDSS; [27]], item 8, rating 2)

• Severe symptomatic exacerbation, defined by the Clinical Global Impression Scale (CGI) which includes ratings of illness severity, changes in overall clinical status, and therapeutic effects. A rating of CGI2 ≥ 6 and CGI 1≥ 6 would be regarded as severe adverse event.

Information about these safety parameters is recorded in the CRF every four weeks by the study rater as part of the regular clinical assessment.

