***Safety***											

Severe Adverse Event asessment^1^		x	x	x	x	x	x	x	x	x	x

CDSS [27]	x	x	x	x	x	x	x	x	x	x	x

Clincal Global Impression (CGI)		x	x	x	x	x	x	x	x	x	x

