Severe adverse events to be observed at every assessment throughout the trial are:

• Death caused by suicide

• Suicide attempt

• Suicidal crisis (explicit plan for serious suicidal activity without suicide attempt) as defined in Calgary Depression Rating Scale for Schizophrenia [CDSS; [27]], item 8, rating 2)

• Severe symptomatic exacerbation, defined by the Clinical Global Impression Scale (CGI) which includes ratings of illness severity, changes in overall clinical status, and therapeutic effects. A rating of CGI2 ≥ 6 and CGI 1≥ 6 would be regarded as severe adverse event.

The safety parameters are part of the regular clinical follow-up examination conducted by the study rater every four weeks. In addition, study participants remain in their usual routine outpatient treatment and will therefore see their independent psychiatrist regularly. The routine care psychiatrist and the study therapist are requested to exchange information about the status of the patient and to provide an optimal individual treatment. The study rater will communicate any information about adverse events to the routine care psychiatrist and the study therapist. Thus, the study provides an optimal framework to immediately detect any complication in the treatment.

Information about the safety parameters is recorded in the CRF every four weeks by the study rater. In addition, therapists are requested to assess the safety parameters in every session and to record their assessment in the session protocol.

The observation of these events should result in a statistical remarkable result, if the incidence of events in one of the two groups will be higher than in the other group. The statistical observation will be done for a significance level of α = 0.2 (two sided) and a power of 0.8 with the help of the software PEST (distributed by Whitehead).

Analyses will be conducted three times: after 100, 200 and 300 patients reaching T3. When analysing the safety data, the full observation period of all patients and all available data will be considered. The safety analyses will be conducted by a statistician (CE) not involved in the design and analysis of this trial, using coded group labels A and B blinded for the real therapy groups.

The results will be reported directly to the members of the independent advisory board. In case of rejection of the null hypothesis of equal incidence rates in the two groups, the advisory board will decide whether or not the study has to be stopped.

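### Deaths not due to suicide and psychiatric admissions lie outside the event list that feeds the three between-arm safety comparisons

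*Protocol article*

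**What the plan says.** The sections Endpoints of Safety and Assessment of safety of interventions during the treatment phase carry the same four-item list:

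- "Death caused by suicide"
- "Suicide attempt"
- suicidal crisis, tied to item 8 of the CDSS at rating 2
- severe symptomatic exacerbation on the CGI: "A rating of CGI2 ≥ 6 and CGI 1≥ 6 would be regarded as severe adverse event"

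The CGI is described as a scale "which includes ratings of illness severity, changes in overall clinical status, and therapeutic effects". Neither list is worded as a set of examples.

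Raters record these parameters every four weeks, and therapists assess them in every session. A statistician outside the trial team compares their incidence between coded groups after 100, 200 and 300 patients have reached T3, at a two-sided 0.2 level. Each look uses the whole observation period and all available data. If equal incidence is rejected, the advisory board decides about stopping.

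Elsewhere, the section on formal characteristics of the therapies makes provision for admissions: "In the case of interruptions of the study therapies due to rehospitalisation of patients", treatment resumes as soon as possible, up to nine months after inclusion. Table 2 schedules the CSSRI at T0, T3, T6, T9 and all four follow-up visits, and the Cost effectiveness section assigns it to the economic project. Table 2 leaves the CGI cell at T0 empty.

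**The concern.** The article sets its own standard in Open questions: "Negative effects should actively be sought in order to demonstrate safety of the treatment". The safety section names therapeutic overstimulation leading to more positive symptoms as the first major risk and summarises earlier evidence in terms of suicide and relapse. The Discussion claims that the trial will be the first to give detailed safety information on CBT for persistent positive symptoms.

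Against that standard the list has two gaps. A death counts only if it is attributed to suicide, so a death of uncertain cause drops out of the comparison. An admission for psychosis counts only if a CGI rating also meets both thresholds. Admission is a hard event that needs no rating on the day, and it is a common sign of the deterioration that the trial is watching for. If these events differed between arms, the comparison given to the advisory board would not show it directly.

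A third, lesser matter is whether a rule that includes a change rating can be checked when no CGI was recorded at entry.

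**Working it through.** The plan states no event rate or detectable difference for the safety test, so there is no figure to reproduce. The check sets the sections side by side.

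**1. Where each kind of event goes when the plan is followed as written**

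| Event | On the four-item list? | Recorded elsewhere? |
|---|---|---|
| Suicide, attempt, crisis | yes | not needed |
| Death of other or undetermined cause | no | no provision stated |
| Psychiatric admission as such | no | service use on the CSSRI, for the cost project |
| Worsening with both CGI items at 6 or more | yes | not needed |
| Worsening with admission, but no rating meeting both CGI thresholds | no | CSSRI only |

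Data Management uses the same term, severe adverse event, for fax reporting. The Table 2 footnote describes the event assessment only as suicide and suicide attempts. Nothing in the article widens the list.

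**2. How far session-level recording helps**

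There are 7 sessions in the first 7 weeks and then 13 fortnightly ones, 7 + 13 = 20 in all. While they run, a therapist sees the patient more often than the rater does. Three limits remain:

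- Therapists assess the same four parameters, so the list is no wider.
- Sessions are interrupted by rehospitalisation, which is when the information matters most.
- Study therapy ends at month 9. The remaining visits are at months 15, 21, 27 and 33, six months apart, while the looks cover the full observation period. An exacerbation that resolves between two of these visits may never receive a CGI rating.

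**3. CGI at T0**

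Table 2 has 11 assessment columns. The CGI row has 10 marks, with T0 empty. The CDSS, PANSS and GAF rows have 11 each. That CGI2 is the change item is inferred from the order in which the article names the components.

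**4. Size**

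The loss cannot be calculated from the document. To show direction only, assume true rates of all serious events of 10% and 18% with 165 per arm, a two-sided 0.2 level (z = 1.2816), and an event list that captures a share s of events equally in both arms. As a fixed-sample approximation,

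power = Φ[(Δ − 1.2816 × SE0) / SE1],

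where SE0 uses the pooled rate and SE1 the separate rates.

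- s = 1: (0.080 − 1.2816 × 0.0382) / 0.0379 = 0.82, power about 79%
- s = 0.75 (7.5% against 13.5%): (0.060 − 1.2816 × 0.0338) / 0.0336 = 0.50, power about 69%
- s = 0.5 (5% against 9%): (0.040 − 1.2816 × 0.0281) / 0.0280 = 0.14, power about 56%

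This shows that a narrow list could weaken the comparison. It does not show that this one does, because both the rates and s are assumed.

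**The case against.** The strongest defence is that the list follows the stated risks. Exacerbation is item four, and suicidality is covered by the other three. Rated worsening is a defensible choice over admission, which depends partly on local practice. Therapists check at every session, the routine psychiatrist and the therapist exchange information, and the looks use all available data. The article also condenses a fuller protocol and states GCP conduct, so a wider definition of reportable events may exist there.

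Much of this stands, and it rules out several stronger readings. A reader might infer that only suicide deaths and exacerbations count, but attempts and crises are listed too. A reader might infer that events are caught only at rater visits, which the session-level recording contradicts. Admissions are also not unrecorded; they are left out of the safety comparison.

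On the CGI, a change item cannot be rated at T0, so a blank there is partly expected. The rule needs both items, so high severity already present at entry is not an event without a matching change rating. PANSS, CDSS and GAF at T0 supply a reference. The baseline worry is largely met.

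The defence does not reach the main point. Both lists are written as complete, and the formal comparison is stated to rest on those events.

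**Conclusion.** The point holds as a design weakness that is cheap to mend. It is neither a contradiction nor a numerical error. Followed as written, the three between-arm comparisons exclude deaths of other or undetermined cause, and they exclude psychiatric admissions unless a CGI rating also meets both thresholds. Session-level recording narrows this gap during treatment but not during admissions or in the follow-up phase.

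The missing T0 CGI is a separate and minor matter. It may be tempting to see it as the reason why deaths and admissions are missed. The documents do not support that: those events are missed because the list omits them.

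No count of missed events can be given, since the article states no admission, death or missed-visit rates. The conclusion assumes that the full protocol does not define the compared events more widely than the article does.

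**What to change.** Set the following before group labels are opened:

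1. Count every death in the safety comparison, with suicide and other or undetermined cause as sub-categories. Cost: one cause category per death, and confirmation of vital status for patients who left the study.
2. Report psychiatric admissions by arm from the CSSRI as a separate safety component next to the four listed events. Restrict to admissions for psychotic worsening only if the reason is recorded; the article says only that overall resource use is assessed. Downsides: admissions partly reflect local practice, so they should stay visible as their own line, and the CSSRI is only three-monthly during treatment and is itself collected at visits.
3. Report the PANSS positive change from T0 beside each CGI-defined exacerbation. A T0 CGI can no longer be obtained, as recruitment closed in January 2010. Cost: a listing from data already scheduled.

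On timing, patients enrolled in January 2010 reach T3 (three months) by about April 2010, so some or all of the three looks may already be past. The change then applies to any look still open and to the final safety report, including follow-up data collected until October 2012.

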### Time schedule of the study and duration of subject participation

Table 4 gives an overview over major phases of this trial. A long preparation phase was necessary due to the multicenter design and the requirements of a publicly funded clinical trial. The recruitment phase was completed in January 2010. The recruitment phase had to be extended as the availability of patients who where willing to give consent was limited in some study centers. However, the designed sample size could be included and the post-treatment assessments (T9) will be finalized in October 2010. Analyses of major outcome will begin in November 2010. Long-term follow-up data will be collected until October 2012.

**Table 4 T4:** Study phases

Phase	Time
Grant application and preparation	March 2005 - March 2007
Recruitment	April 2007 - January 2010
Treatment completion and completion of post treatment assessment	February 2010 - October 2010
Follow-up until 24 months after treatment	November 2010 - October 2012
Start of Analysis of primary outcomes	November 2010

A single patient participates for a duration of 33 months consisting of the treatment phase (9 month) and the follow-up phase (24 months). The time of "first patient in" until "last patient out" will be 67 months.

## Associated research

### Cognitive deficits and biases

For the assessment of neurocognitive deficits, a short and reliable neuropsychological battery consisting of tests measuring verbal intelligence, attention, executive functions, and memory is administered. This battery has been widely employed in the BMBF funded German Research Network on Schizophrenia [53] and a substantial database on the relationship of cognitive deficits with psychopathological symptoms, course of illness, and response to therapy has been gathered [54]. The assessment of cognitive biases or cognitive styles is an emerging field of research, and several experimental studies have found evidence of specifically altered performance in delusional subjects [55,56]. Therefore, the sub-processes of social cognition which might serve as mediating mechanisms will be assessed in detail in the sub-project "Cognitive deficits and cognitive biases underlying delusional symptoms and therapeutic change" (PI: MW). Attribution style is assessed with the Internal, Personal and Situational Attribution Questionnaire [IPSAQ; [57]]. Usually, the attributional style of paranoid patients is altered in that they, similar to depressed patients, make global and stable explanations for negative events, but, unlike depressives, they preferentially assume external causes, and particularly other people to be responsible [8]. Another aspect of disturbed inferential thinking relates to the evaluation of hypotheses. In tasks requiring one to make a good guess based on prior evidence, paranoid patients jump to conclusions prematurely, as if they need less evidence to be sure (this style has been termed epistemological impulsivity). One method to assess such a reasoning style is the Beads in a Jar Task of Garety and colleagues [58]; an adapted computer version of this task [59] is employed here. Finally, standardized pictures from the Pictures of Facial Affect set [PFA; [60]] are applied to assess accuracy and speed of facial affect recognition.

### Neural correlates of cognitive biases

A functional magnetic resonance imaging (fMRI) study (PI: TK) investigates major mediating factors of Blackwood's model. Using fMRI differential effects of CBT and ST on cerebral activation is being investigated. The present study investigates neurophysiological processes underlying the development and amelioration of symptoms of delusion. The neural correlates of jumping to conclusions and attributional bias will be investigated. The paradigms of the fMRI study will be complementary to those applied in a larger sample via neuropsychological experiments outside the scanner. Extensive reliability and quality control measurements ensure the validity of data across different centres. The following questions will be addressed: What are the neural correlates of delusions taped by the dysfunctional processes of attributional bias and jumping to conclusions? Can future therapeutic success be predicted on the basis of specific brain activation patterns already before treatment? Which components of neural circuits can potentially by altered by CBT? Are there distinct brain structures that can be linked to delusions?

### Cost effectiveness

An associated project assesses the cost effectiveness of the treatment (PI: HHK). The direct and indirect costs of both study arms are calculated prior, during and after therapy using a modified version of the „Client Sociodemographic and Service Receipt Inventory" [61]. The CSSRI assesses the overall resource utilization of patients as well as productivity losses. To estimate costs these quantities are then valued with market prices. When market prices are not available administrative prices or mean costs are used to estimate so called "shadow prices".

To assess the health effects of CBT and ST, two different measures are used. On the one hand the EQ-5D [62], a generic measure of subjective health related quality of life comprising a health profile and a visual analogue scale is used prior, during and after therapy. From the EQ-5 D, health state utilities are derived to calculate quality adjusted life years (QALYs) [63]. On the other hand an objective measure of positive symptoms (PANSS-Score) is used to quantify treatment response.

A Markov model is built to estimate the ICER using long term costs and effects beyond the time frame of the study. Markov models simulate the course of a disease over time and thus allows for calculating long term costs and effects.

### Adaptation of CBT for adolescents

This sub-project (principal investigator: AB) represents a pilot study which focuses on the evaluation of extensions of CBT for adolescents with early onset psychosis (EOP). Objectives are to develop a modified CBT (mCBT) for adolescents with EOP, to explore its acceptance and feasibility and to provide data for a realistic estimation of achievable effect size. The study is a multicenter, prospective, parallel group, randomised controlled trial. Forty-two patients will be recruited. All participants will receive individual optimised psychiatric treatment as usual (TAU). mCBT will be provided for 50% of the patients (n = 21) in addition to TAU. mCBT is an outpatient treatment which consists of 20 individual sessions in nine months and five psychoeducation sessions with parents. All sessions will be conducted by specifically trained psychotherapists on the basis of a treatment manual.

The primary endpoint will be the positive syndrome of the PANSS at T9 (post treatment assessment). Monthly assessments during the treatment phase will closely monitor the course of symptoms. Patients have to fulfil DSM-IV criteria of schizophrenia, schizoaffective disorder, or delusional disorder, confirmed by a structured clinical interview (SCID-I). Decisive for inclusion is a score of 4 or more on the PANSS-items "Delusions" (P1) or "Hallucinations" (P3) or „Unusual thought content" (G9) representing a moderate or severe symptom intensity. Furthermore the presence of positive symptoms for at least four weeks or more is necessary.

## Discussion

### Relevance of the POSITIVE study

This clinical trial is part of efforts to intensify psychotherapy research in the field of psychosis in Germany, to contribute to the international discussion on psychotherapy in psychotic disorders, and to help implement psychotherapy in routine care. Furthermore, the study will allow drawing conclusions about the mediators of treatment effects of CBT of psychotic disorders.

In an innovative approach the network combines clinical trials on the efficacy of CBT with research designed to analyse active ingredients of the treatment. The POSITIVE Study will presumably be the largest full scale clinical trial comparing CBT with ST. This comparison will allow drawing conclusions about the specific efficacy of CBT for the treatment of persistent positive symptoms in psychotic disorders. The projects of the research network will give information about the processes of CBT, the effects of CBT on cognitive biases as well as the neural basis of theses biases. The latter have not yet been studied, in particular with respect to treatment outcome. Further, a full economic evaluation of CBT will be conducted. To this day, no such data on cost effectiveness are available yet.

